### Footwear insole interventions

Two footwear insole interventions will be utilized within the experimental arm of this study: (1) the first is a medial wedge insole placed within the participants own shoe. The insole will be developed using a 3D printer, where the wedge thickness is 0.5 mm on the lateral edge, and 6.5 mm on the medial edge. The insole will taper at the metatarsal heads to a thickness of 4.5 mm to ensure a comfortable fit within the participant’s shoe. A wedge thickness of about 6 mm has been used previously and has been shown to be large enough to influence knee mechanics, yet small enough to maintain comfort [14, 19–21]. During testing and long term use, this insole will be placed under the existing sock liner of the participant’s shoe. (2) The second condition is a lateral wedge insole placed within the participants own shoe. The insole will be developed using a 3D printer, where the thickness of the medial edge is 0.5 mm and the thickness of the lateral edge is 6.5 mm, tapering to 4.5 mm beyond the metatarsal heads. During testing and long term use, this insole will be placed under the existing sock liner of the participant’s shoe. For construction of the medial and lateral wedge, the wedge will extend along the full length of the foot, creating approximately 5–6 degree medial and lateral wedges [22]. All insoles will be produced by New Balance Athletic Shoe Inc. (Boston, MA). The material utilized for the insoles is stiff in compression, such that the wedge shape will be maintained throughout the 3 month study; however, the material is also flexible to ensure comfort within the shoe during flexion of the metatarsal joints.

The authors must emphasize the relationship between the intervention we intend to utilize (wedged insoles), and the mechanical effect we aim to achieve (reduced KAMs). It is this mechanical result (reduced KAMs) that is suggested in the literature to affect knee OA – not wedged insoles on their own. Thus it is critical to bear in mind that the wedged insoles are simply a means to achieve the desired mechanical outcome.

Recently, it has been reported by a meta-analysis that future knee OA trials should utilize a flat insole as a control condition [16]. The motivation for this claim was based on the notion that this would control for placebo effects. However, recent evidence has suggested that even flat insoles can alter pressure distributions under the foot during gait [23], and thus it remains a possibility that KAMs could be influenced as well. Therefore, while flat insoles may control for placebo effects, they may not control for gait biomechanics, which is the primary concern of our trial. Consequently, the control condition for our study will be the participant’s own footwear, as this will control for gait biomechanics changes. Therefore, for biomechanical reasons, the trial will not be placebo controlled. In effort to ensure recruitment, compliance and participant retention in our control condition, we will utilize a waitlist control strategy, where we will indicate that a 3 month wait is required prior to providing an insole. After 3 months, we will provide control participants with access to a wedged insole, and continue to monitor them for safety.

### Laboratory testing protocol

All eligible participants will be invited to the laboratory for baseline testing. At baseline, body metrics such as height (m), mass (kg) and age (years) will be recorded, and also basic clinical diagnostic data (eg. Kellgren-Lawrence grade).

#### Body composition

Lean and fat mass will be evaluated at baseline using Dual Energy X-Ray Absorptiometry (DXA, Hologic QDR 4500; Hologic, Bedford, MA), the clinical gold standard for body composition.

#### Biomechanics

Eight Motion Analysis cameras (Motion Analysis Corp., Santa Rosa, CA) sampling at 240 Hz will record the 3D trajectories of retroreflective markers placed over the participants most symptomatic limb as they walk along a 20 m runway. A force platform (Kistler AG, Winterthur, Switzerland) will collect ground reaction force data at a frequency of 2400 Hz as the participant walks along the runway. This will be done for 5 successful trials in each of 3 footwear conditions for each participant: (1) participant’s own shoe (baseline condition), (2) participant’s own shoe with the lateral wedge insole, and (3) participant’s own shoe with the medial wedge insole. A successful trial is defined as one where the participant lands with their most symptomatic limb near the center of the force platform, does not touch the force platform with their other limb, and maintains a gait speed of 1.3 ± 0.07 m/s as measured by two photocells.

Kinetic and kinematic data will be filtered using 4^th^ order Butterworth low-pass filters with cut-off frequencies of 50 Hz and 12 Hz, respectively. KAMs during stance will be calculated using an inverse dynamics approach, and the peak KAM (first peak) will be identified for each trial [4, 19]. The average KAM across trials for each footwear condition will then be calculated and represented as a percent change from the baseline condition value. The KAM impulse (integral of KAMs with respect to time) and Varus thrust (maximum mediolateral displacement of knee joint center from touchdown) [24] and the KAM impulse (integral of KAMs with respect to time) [25] will also be calculated as these variables have also been shown to be related to knee OA [6, 24]. At the baseline visit, biomechanical testing and DXA scans will be performed and survey information will be collected. After determining the peak KAMs for all three conditions, the percent change in KAM will be determined for the medial and lateral wedge conditions.

### Survey protocol

#### Patient history

Detailed musculoskeletal injury histories will be taken for each participant. This will be done on a recall basis, and will specifically request that patients outline any previous traumatic, acute knee injuries (e.g. meniscal injury, patellofemoral injury, proximal tibial or distal femoral fractures, plica, knee ligament damage including avulsion tears, or any large impacts to the knee causing excessive bruising or swelling), surgical procedures on the knee, or any history of heavy loading activities (e.g. American football, running, ski jumping etc.).

#### KOOS

The Knee Injury and Osteoarthritis Outcomes Score (KOOS) is based on the Western Ontario and McMaster Universities (WOMAC) Arthritis Index– a survey that is both valid and reliable for measurement of pain, function and stiffness in OA populations [26–32]. Additionally, the KOOS includes subscales that can evaluate function in activities of daily living and during more rigorous activity, allowing it to be sensitive to differences in activity between individuals. The five KOOS components include: pain, symptoms, function in daily living, function in sport and recreation, and knee related quality of life. The KOOS has been extensively validated and can be used over long periods of time, allowing for possibility of long-term follow-up of the recruited patient cohort [33–37]. The KOOS will be administered at baseline, and at 1 month, 2 months and 3 months follow-up.

#### Physical activity

Two physical activity scales will be used in this study. The first is the UCLA physical activity scale. This scale provides a global measure of activity, and is commonly used in osteoarthritis populations undergoing arthroplasty [38]. The second is the Physical Activity Scale for the Elderly (PASE). PASE will be used to evaluate the type and duration of recreational and occupational physical activity of the previous week [39]. This scale was originally developed and validated for individuals over the age of 55 years, which is appropriate for the majority of the knee OA population. The purpose of the physical activity scales are to identify whether physical activity levels generally increased, decreased or remained constant during the study for experimental and control participants. The tests will be administered at baseline, and at 1 month, 2 months and 3 months follow-up.

#### Adherence

At baseline, participants will be asked to refrain from utilizing any alternate therapies during the study period (aside from anti-inflammatory or acetaminophen medication), and asked to utilize the prescribed footwear condition as frequently as possible during the day. While not an exclusion criteria of this study, participants will be asked to try and always use the insole in the same shoe tested at baseline. We will conduct a survey at 1 month, 2 months and 3 months follow-up to evaluate participant adherence to the intervention, which will include recall of the number of hours per day using the assigned insole over the past week, recall of the number of times in the past week a different shoe from baseline was used with the insole, and recall of the number of times alternate allowable therapies were used, such as targeted exercise for OA or anti-inflammatory and acetaminophen medications. Use of therapies that are considered as exclusion criteria (i.e. viscosupplementation, knee braces, narcotic pain medication), will also be recorded.

#### Comfort

Some studies have suggested that footwear comfort may be an important variable in determining the effectiveness of a footwear intervention on pain management [40]. Therefore, we will administer a paper-based 100 mm visual analog scale with the terms “extremely comfortable” and “extremely uncomfortable” as anchors at 100 mm and 0 mm, respectively. The tests will be administered on paper at baseline.

### Randomization

Following the baseline laboratory and survey testing, participants will be randomized into one of two study arms: (1) a KAM-reduction experimental group (KAM-R), or (2) a waitlist control group. In the KAM-R group, participants will be given either a medial or lateral wedge insole (whichever insole reduces KAMs more for each individual participant) to put inside their own shoe and use for 3 months. In the waitlist control group, participants will be asked to continue using their own shoes for a period of 3 months, and following this will be provided with access to a wedged insole (whichever reduces KAMs more based on baseline data collection).

Participants will be randomized using a multi-block-randomization procedure into either the KAM-R or waitlist control group. Specifically, a separate block sequence will be used for males and females to ensure an even sex distribution across groups. A block size of 6 will be used for each, and the sequence will be determined from a random number generator.

The one exception to this block randomization procedure is that if neither wedged insole produces a KAM reduction, the participant will be excluded from the main study altogether. This scenario will not be common, as most people do experience a large change in KAMs with one of the two wedged insole types, but this strategy will ensure that all participants in the KAM-R and waitlist control groups are all biomechanically suitable for a wedged insole intervention. Thus, neither group will contain biomechanical non-responders to wedged insoles.

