### Blinding

Knowledge of the participant’s KAM change is required to ensure that the study sample consists entirely of those who experience a reduction in KAMs with at least one insole type. We will randomize patients to either the KAM-R or control group prior to knowing the KAM results and prior to any data collection. After collecting biomechanical data, KAM results will be assessed to verify that the participant experienced a KAM reduction in at least one wedged insole type. As described previously, in cases where the participant does not experience a KAM reduction with either insole, they will be excluded from the main study. Thus our knowledge of KAM changes will not affect our initial randomization, and only be used as a verification tool. Although researchers will be aware of each participant’s study group following randomization (in order to assign the participants in the KAM-R group an insole to take home), the researchers will be blinded during future survey data collection and data analysis as identifying information will be stripped by an independent researcher and replaced with unique patient ID numbers and numerical values for group allocation. Those involved in statistical analysis will be blinded to the group allocation and outcomes during data analysis. All KAM-R participants will be aware as to which condition they have been assigned, based on knowing that they have received an insole. All control condition participants will be aware that they have not received an insole at baseline, but will receive an insole at 3 months. Thus, the study will not be blinded at baseline data collection; however, follow-up data collection and data analysis will be blinded to the researchers.

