### Sample size calculation

Sample size calculations were performed based on our primary outcome variable, the KOOS pain score, with a desired power of 80% and a significance level of 0.05 using the statistical software Stata version 11.2. Given the early stage of research concerning the effects and interactions of load reduction, and different OA subtypes on treatment outcome, we chose to only conduct sample size calculations on a repeated measures basis for within group comparisons. Based on the results of this trial, sample sizes may be expanded to increase statistical power in order to make comparisons between the control and KAM-R group.

The minimum perceptible clinical improvement and minimum detectible change in KOOS score has been reported to be about 13.4 points [33, 41]. Using a baseline KOOS pain score of 57.3 points [42] and a standard deviation of 15 points [41], to detect a minimal clinically important improvement of 13.4 points within each group, 20 participants are required in each group, or 40 total participants. To account for a potential dropout rate of 15%, we will recruit a minimum of 46 participants.

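### A constant block size of 6 within each sex, with researchers aware of past allocations, could let someone tracking a stratum know about 22–23% of the 46 assignments in advance

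*Protocol article*

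**What the plan says.** The Randomization section of the protocol article describes a two-arm blocked scheme: "Participants will be randomized using a multi-block-randomization procedure into either the KAM-R or waitlist control group". It is stratified by sex only: "a separate block sequence will be used for males and females to ensure an even sex distribution across groups". The block length is a single constant: "A block size of 6 will be used for each, and the sequence will be determined from a random number generator". No ratio within blocks is written there, but the Sample size calculation section plans equal arms ("20 participants are required in each group, or 40 total participants") and a recruitment minimum of 46.

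The Blinding section says that "researchers will be aware of each participant’s study group following randomization", because they have to issue the insoles. Participants know their arm as well: "All KAM-R participants will be aware as to which condition they have been assigned", and controls know that they have no insole yet. Removal of identifiers protects follow-up surveys and the analysis. It does not reach back to entry: "Thus, the study will not be blinded at baseline data collection".

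The two sections give different orders of events. The Randomization section places allocation after the baseline laboratory and survey tests. The Blinding section places it ahead of all measurement, and then says that "in cases where the participant does not experience a KAM reduction with either insole, they will be excluded from the main study".

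**The concern.** In a permuted block of known, constant length, the last places follow from the earlier ones. Here there are only two sequences to follow, and the staff who issue insoles see each allocation as it is made. Someone in that position could know the next arm before deciding whether, or when, to bring in the next patient.

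Selection of this kind acts before allocation, so masking of follow-up surveys and analysis cannot undo it. It would matter here because the primary outcome is the KOOS pain score, reported by patients who know their arm. The KOOS pain score is also an entry criterion, so it is known when a patient is considered. Each arm has about 20 patients, so a few selective enrolments would carry weight.

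**Working it through.** The article gives no figure for predictability, so there is none to reproduce. The total used below is its own: 40 × 1.15 = 46.

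**Inputs.** Block size 6, two sex strata and two arms (Randomization); equal arms (Sample size calculation), taken to mean 3 + 3 per block; 46 participants. The split by sex is not given, so every split of 46 was examined.

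**Step 1: one complete block.** There are C(6,3) = 20 equally likely orders. An assignment is certain once one arm has used its three places.
- Places 1 to 3: probability 0.
- Place 4: the first three are all the same arm, 2/20 = 1/10.
- Place 5: one arm has three of the first four, 2 × 4/20 = 2/5.
- Place 6: always, 1.

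The sum is 0.1 + 0.4 + 1 = 1.5 certain assignments per block, and 1.5/6 = 25%. The general formula for a block of 2k gives the same: 1/(k + 1) = 1/4 for k = 3.

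**Step 2: the planned 46, with unfinished last blocks.**
- Split 23/23: each sex has three full blocks plus five places, 3 × 1.5 + 0.1 + 0.4 = 5.0. The total is 10.0, and 10.0/46 = 21.7%.
- Split 22/24: 3 × 1.5 + 0.1 = 4.6 and 4 × 1.5 = 6.0. The total is 10.6, and 10.6/46 = 23.0%.

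These are the lowest and highest values over all splits of 46.

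**Step 3: guessing short of certainty.** Always guessing the arm with more places left gives, per block, k + (2^(2k)/C(2k,k) − 1)/2 = 3 + (64/20 − 1)/2 = 4.1 correct. That is 4.1/6 = 68.3%, against 50% by chance.

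**Step 4: randomly varying block sizes.** Simulation with 20,000 sequences per stratum of 23 or 24. The observer knows which sizes are possible, but not their order.

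| Block sizes | Certain (23 / 24 per stratum) | Best guess correct (23 / 24 per stratum) |
|---|---|---|
| 6 only | 21.7% / 25.0% | 67.0% / 68.3% |
| 4, 6 | 5.7% / 5.8% | 68.2% / 68.7% |
| 2, 4, 6 | 3.7% / 3.8% | 69.2% / 69.7% |
| 4, 6, 8 | 2.3% / 2.4% | 66.9% / 67.3% |

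With sizes 4, 6 and 8, about 1 of 46 assignments is certain (46 × 0.023 ≈ 1.1) instead of about 10. Best-guess success hardly moves.

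**Step 5: order of events.** If allocation follows baseline testing, block deduction could inform both enrolment and the KAM exclusion. If allocation comes first, the group may be known outright when the exclusion is decided. Deduction then matters for enrolment only, and block length has no bearing on the exclusion. Participants excluded after allocation would still have used places in their block, and an observer who saw them could count them.

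**The case against.** The percentages describe a conditional case. They need one person who knows the block length, follows every allocation in a sex stratum and can influence who enters or when. The article does not put one person in that position. Patients come from a sport medicine centre and arthroplasty clinics, a physician makes the diagnosis, and those said to know allocations are the researchers issuing insoles. Overlap is plausible at one laboratory but is not stated. A block size printed in an article is also not the same as one told to recruiting staff. This stands, and the conclusion is worded accordingly.

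A reader might infer that allocation is not concealed. The article does not support that. It says nothing on who holds the list or how assignments are released, and an article commonly leaves this to the full protocol. The criticism rests only on the stated constant block size. A sealed list would not by itself cure that, because the end of a block is deduced from known allocations and not read from the list.

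A reader might also infer that varying the sizes makes allocation unpredictable, or that the KOOS result will be biased. Step 4 contradicts the first. For the second, the article offers no evidence of steering and no basis for a bias in KOOS points. As a pure illustration, if 3 of 20 patients in one arm differed by 15 points (the article's SD), that arm's mean would move 3 × 15/20 = 2.25 points, against the 13.4-point target.

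Finally, between-group comparisons are declared exploratory and the sample size is described as a within-group one. This lowers the stakes without removing them: the Background hypothesis compares the groups, and selective entry into the KAM-R arm would also affect its within-group change.

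**Conclusion.** The point holds as an avoidable weakness in a stated rule. Under 1:1 blocks, someone who knows the block size and tracks allocations within a sex could expect to know 10.0 to 10.6 of the 46 assignments with certainty (21.7% to 23.0%; 25% in complete blocks). It would be too strong to say that these assignments are in fact known in advance, or that the trial lacks concealment.

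The gain from varying block sizes is the loss of most of the certainty, down to about 2%. It does not lower best-guess success, which stays near 67%. Separately, the Randomization and Blinding sections contradict each other on the timing of allocation. That conflict decides whether the KAM exclusion is made with the group already known.

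**What to change.** Before enrolment, generate a new list with block sizes varying at random within each sex, for example 4, 6 and 8, and do not disclose the sizes to staff who recruit or test. In the Randomization section, replace the fixed size with a statement that sizes vary and are withheld from those staff.

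The work is one computer-generated list. The downside is a slightly larger possible imbalance when recruitment stops inside a block: at most 8/2 = 4 per sex instead of 6/2 = 3, so 8 instead of 6 over both sexes in the worst case.

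Reconcile the Randomization and Blinding sections so that both give the same order for allocation, baseline testing and the KAM exclusion. Varying the block sizes cannot substitute for this, since it does nothing for an exclusion decided after the allocation is known.

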## Discussion

The primary goal of this randomized controlled trial is to identify the influence of reduced KAMs on management of knee OA symptoms. In this study, wedged footwear insoles will be used as the intervention to induce reduced KAMs. Wedged insoles are a relatively inexpensive and easy-to-use intervention, and have been a recommended management strategy in numerous international clinical guidelines for OA. However, some randomized trials conducted on wedged insoles have shown inconsistent results. The primary reason for this is that previous studies used exclusively a lateral wedge insole and did not test each participant’s biomechanics to ensure that the lateral wedge actually reduced KAMs. Indeed, it has been found in numerous studies that lateral wedges may in fact increase KAMs during gait for some participants, which could induce OA worsening, and wash out any actual treatment effects of reduced KAMs that may be observed in other participants [12, 13]. Thus, in our study, we are testing both medial and lateral wedge insoles, and prescribing the insole that reduces KAMs the most. This will ensure that all participants in our KAM-R group experience reduced KAMs.

Another reason why other wedged insole studies have shown mixed results on OA management is that these studies used inadequate control interventions. Specifically, some studies have given all control participants a flat neutral insole. Other studies have provided a new shoe to all participants as a control condition [40]. While in theory this is appropriate as an attempt to protect against placebo effects and provided a method for blinding, it does carry the possibility that some participants will experience altered KAMs during gait. For instance, McCormick et al. [23] have shown that control insoles alter pressure distributions relative to a no insole condition, and this pressure shift could affect KAM magnitude [4]. Therefore, in our study, we have chosen to utilize the participant’s own shoe as a control condition to ensure biomechanics remain unchanged. Our regression analyses will provide some insight into whether placebo effects do exist with wedged insoles. For instance, if the slope of the line of best fit is not near zero, it would suggest that change is pain is related to a reduction in KAM regardless of whether a placebo effect exists or not.

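### The KAM screen shows an observed drop at one session and does not assure a true reduction, so the no-non-responders guarantee and the one-tailed KAM tests lack support.

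*Protocol article*

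**What the plan says.** The rule is spread over three Methods sections of the protocol article.

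- **Measurement (Biomechanics).** Walks are recorded at the baseline visit: "This will be done for 5 successful trials in each of 3 footwear conditions for each participant". The response measure is peak KAM: "The average KAM across trials for each footwear condition will then be calculated and represented as a percent change from the baseline condition value". Both wedges are thus compared with one own-shoe mean.
- **Screen (Randomization, Blinding).** A participant leaves only under one condition: "if neither wedged insole produces a KAM reduction, the participant will be excluded from the main study altogether". The Blinding section puts it the other way round: "KAM results will be assessed to verify that the participant experienced a KAM reduction in at least one wedged insole type". No minimum reduction, error allowance or repeat test is attached.
- **Wedge choice (Randomization).** The assigned wedge is "whichever insole reduces KAMs more for each individual participant", judged on the same walks.

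The article draws firm conclusions from this. Randomization states "Thus, neither group will contain biomechanical non-responders to wedged insoles". The Discussion says of prescribing the better wedge: "This will ensure that all participants in our KAM-R group experience reduced KAMs". Both the within-group and the between-group analysis sections justify one-tailed tests of KAM and KAM impulse on the ground that only a decrease can occur.

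**The concern.** The screen takes the more favourable of two measured changes and compares it with zero. Each change is a difference of two five-walk means, so each carries error. A value below zero can come from a true reduction or from error, and having two chances favours passing.

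Three uses of the data depend on the reduction being real:

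1. Assured KAM reduction is the stated advance over earlier insole trials. If it is only observed, a null pain result could mean that reducing KAM does not help, or that KAM was not reduced in some participants.
2. The paired KAM test in the insole group is run on the data that selected both participant and wedge.
3. KAM change is a predictor of pain change in the regression, and the Discussion uses the slope of that line to comment on placebo effects.

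**Working it through.** The article gives no error rate for the screen, so there is no stated figure to reproduce.

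**Inputs from the article:** three conditions, five walks each, one visit, one shared own-shoe mean, cut-off at any drop, better of two wedges, 46 recruited.

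**Assumptions:** equal, independent, normal error in the three condition means. The walk-to-walk SD of peak KAM is not given; 2% to 10% of the own-shoe value is assumed below where it is needed.

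**Step 1. Pass rate with no true effect.** The participant fails only if the own-shoe mean is the lowest of the three means. With no true differences each of the three is equally likely to be lowest, so P(fail) = 1/3 and P(pass) = 2/3. The bivariate normal formula agrees: the two changes correlate at 0.5, so P(both ≥ 0) = 1/4 + arcsin(0.5)/(2π) = 1/3. The SD does not enter. With independent changes the pass rate would be 1 − 1/4 = 3/4, and with one wedge 1/2.

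**Step 2. Apparent reduction among those who pass.** Let s be the error SD of one condition mean, so SE of the change = s√2. The expected minimum of three standard normals is −3/(2√π) = −0.846. The mean reduction, counting those who fail as zero, is therefore 0.846s. Divided by 2/3 this is 1.269s, and 1.269/√2 = 0.90 SE.

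**Step 3. In percent.** SE of the change = SD × √(2/5).

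| Assumed walk-to-walk SD | SE of change | Apparent reduction (0.90 SE) |
|---|---|---|
| 2% | 1.3% | 1.1% |
| 4% | 2.5% | 2.3% |
| 6% | 3.8% | 3.4% |
| 10% | 6.3% | 5.7% |

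**Step 4. Other true effects (simulation).** If both wedges truly raise KAM by 0.5 SE or 1 SE, 45% or 25% pass. If the wedges have opposed true effects of ±1 SE, 1.6% of those who pass receive the KAM-raising wedge. At ±2 SE practically none do, and the reduction is overstated by only about 0.06 SE.

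**Step 5. How many might be enrolled.** Let π be the assumed share of screened patients with no true effect, all others passing. Their share among those enrolled is f = (2π/3)/(2π/3 + 1 − π).

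| π (assumed) | f | Expected among 46 | P(at least one), 1 − (1 − f)^46 |
|---|---|---|---|
| 2% | 1.3% | 0.6 | 46% |
| 5% | 3.4% | 1.6 | 80% |
| 10% | 6.9% | 3.2 | 96% |
| 20% | 14.3% | 6.6 | 99.9% |

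**Step 6. The peak-KAM test in the insole group.** Take 20 participants who passed with no true effect. Their apparent changes average −0.90 SE with a simulated SD of 0.63 SE, so a typical t is −0.90/(0.63/√20) = −6.4. In simulation the one-tailed test at 0.05 rejected in essentially every sample. A significant result therefore does not show that KAM was truly reduced. KAM impulse plays no part in the screen, so a rise in impulse is possible.

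**Step 7. Effect of a cut-off.** The pass rate of a participant with no true effect falls from 66.7% (any drop) to 25.5% at 1 SE, 8.8% at 1.645 SE and 4.5% at 1.96 SE.

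**The case against.** The strongest reply is that a true zero effect of both wedges is the unfavourable case. The wedges are mirror images, and the article says of finding no reduction: "This scenario will not be common, as most people do experience a large change in KAMs with one of the two wedged insole types". Trying both is the designed answer to patients who respond opposite to the average. Step 4 supports this: with opposed effects of 2 SE the screen works well. Walking speed is controlled and five walks are averaged. Both arms pass the same screen, so it creates no imbalance by itself. The Background also states the aim as the effect of a personalised insole on pain, which can still be interpreted. If a non-responder simply means someone with no observed reduction, the sentence is true by definition.

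Most of this stands as a limit on size. It does not rescue the guarantee. The article uses the sentence to assert real biomechanical suitability, and an expected rarity for which no rate is given is not assurance.

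A reader might go further and infer that the guarantee is false, or that most patients without a true reduction get through. The documents support neither. The first needs a prevalence and a reliability that they do not give. The second holds at exactly zero effect (67%) but not when KAM truly rises by 0.5 or 1 SE (45%, 25%).

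**Conclusion.** The concern holds as a limit on what the screen can show. The 2/3 pass rate and the 0.9 SE apparent reduction apply to participants with no true effect of either wedge. They rest on equal, independent error in the three condition means (with normal error for the 0.9 SE). The reduction in percent and the number of such participants enrolled depend on assumed values.

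The claims that neither group holds non-responders, that everyone in the insole group has reduced KAM, and that only a decrease can occur are not assured; they are not shown to be false. If most patients have large opposed effects, few true non-responders will be enrolled.

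Two consequences do not depend on prevalence. The peak-KAM test in the insole group cannot verify reduction, because it reuses the selecting data. The one-tailed rationale for KAM impulse has no basis in a screen that uses peak KAM only. The likely harm is dilution and an overstated KAM reduction, not imbalance between arms. The change should be made, because it affects what a null pain result can be taken to mean.

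**What to change.** Leave enrolment and wedge choice as they are.

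1. Restate the guarantee, in Randomization, Discussion and both analysis sections, as an observed reduction in peak KAM at one session.
2. From the five recorded walks per condition, report each participant's KAM change with its standard error, and the number in each arm whose reduction exceeds a prespecified multiple of it. An example is 1.645 SE, which about 9% of participants with no true effect would still pass.
3. Add a sensitivity analysis of KOOS pain in participants of both arms above that cut-off, labelled exploratory because it will be small.
4. Present the peak-KAM test in the insole group as descriptive and make the KAM impulse test two-sided. State that measurement error in the KAM change attenuates the regression slope, so a slope near zero is weak evidence of no relation.

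Estimating the reduction from split halves of the walks is not recommended. Eligibility and wedge choice already use all five walks, splitting still leaves about 0.53 SE of apparent reduction in participants with no true effect, and it does not remove the attenuation.

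The cost is a little more analysis and a less favourable statement about KAM reduction. No new data are needed.
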